**Before surgery**						
	1	1	What to expect?		The goal is to have a clear understanding of what to expect from the diagnosis, surgery, and health coaching program. The qualified exercise professional will work with the participant to create a list of questions to discuss with their surgeon prior to their next visit. The qualified exercise professional will also start the process of what resources participants might need during their treatment, including Cancer Patient Pharmacare (which covers prescription cessation aids for example), Canadian Cancer Society patient supports (transportation supports), and other potential supportive services.	
	2	1	Understanding your body		The qualified exercise professional will go through how participants know their body the best, and things to look for when doing more movement. Key concepts of this session will be a rating of perceived exertion, use of our environment, and history of physical activity.	
	3	1	Movement + me		Participants will work with qualified exercise professionals to better understand what movement looks like for them and what type of movement they enjoy. Finding movement enjoyable is key to successful long-term movement.	
	4	2	Smoking cessation or sleep hygiene		If a participant reports current tobacco use, the qualified exercise professional will help the participant to understand the importance of smoking cessation as they prepare for surgery. This will include providing information about Tobacco Free NS and assisting with steps to access appropriate cessation resources. As well, participants will discuss sleep quality and the importance of sleep in preparation for and recovery from thoracic surgery.	
	5	2	Mindfulness		The qualified exercise professional will go through basic mindfulness attitudes, including patience, acceptance, and trust. The qualified exercise professional will review techniques for stress reduction and breathing.	
	6	2	Prepping for surgery		The qualified exercise professional will go through a reminder about things to bring with them to the hospital and talk about what to expect in the next few days. Participants will be reminded of the work they have done this far and be given a hospital date for their meet-up.	
**Surger**y						
	7	3	How are you feeling now?		The qualified exercise professional and participant will discuss how they are feeling and what supports the qualified exercise professional can offer to facilitate the transition from hospital to home setting.	
	8	4	Movement at home		The qualified exercise professional will assist the participant in better understanding movement at home and how they can make small movements as part of their everyday life. The focus of this session will be on doing small movement “snacks” and listening to their body.	
	9	5	Goal setting		Qualified exercise professionals will go through SMART^a^ goals with the participants. This will include long- and short-term goals with an understanding of upcoming treatment and how that will affect goals.	
	10	6	Nutrition		The qualified exercise professional will assist the participant in the understanding of food as a whole and how important nutrition is when undergoing treatments for cancer, this will include tips from Canada’s Food Guide. If needed, the qualified exercise professional will also have resources for the food bank and how to access these types of services in their community.	
	11	8	Long-term planning: what is next?		The qualified exercise professional will discuss a long-term plan for the participant to sustain healthy lifestyle habits. They will go through their movement notes together and find a movement plan that will work for this participant, whether that be at home, at a local gym, or a more structured program.	
**Follow-up appointment with surgeon**						
	12	16	Booster session: where we are now?		The qualified exercise professional will discuss how the participant is feeling now and revisit goals. If participants require further support, the qualified exercise professional will also do anything within their scope and also refer to the Community Health Team resources, which offer support on many wellness topics and are free to all Nova Scotia residents.	
	13	24	Booster session: where we are now?		The qualified exercise professional will discuss how the participant is feeling now and revisit goals.	
	14	32	Booster session: where we are now?		The qualified exercise professional will discuss how the participant is feeling now and revisit goals.	

^a^SMART: Specific, measurable, attainable, realistic, time orientated.

#### Movement Programming

All movement programming will be tailored to each individual participant’s current health status, goals, interests, and abilities. Each one-on-one movement session is expected to last 15-45 minutes and will include time for both warmup and cooldown. Participants will be instructed to begin at a light-to-moderate intensity (ie, 3-6 on a 10-point Borg Scale); systematically progress (ie, periodized); and combine aerobic and resistance training programs for 15-45 minutes, 3 days/week. Should a participant feel that any movement is beyond their comfort level or ability, they will be instructed to inform the qualified exercise professional so that the movement can be modified to better suit their needs (Table 2).

**Table 2 table2:** Outline of a movement programming^a^.

	Description	Frequency	Intensity	Type	Time
Warmup	All sessions begin with a 5-minute warmup to gently increase heart rate and mobilize major muscle groups (RPE^b^ 1-3/10).	—^c^	—	—	—
Aerobic	—	3-7× per week (3 supervised and 0-4 unsupervised)	MICT^d^ (3-6 RPE) or HIIT^e^ (7-9/10 RPE)	Rhythmic repetitive movements (eg, walking, marching, cycling)	10-15 minutes
Resistance	—	3× per week	4-7/10 RPE	Targeting major muscle groups including: Legs (eg, sit to stand) Back (eg, horizontal row) Chest (eg, wall pushups) Core (eg, dead bug) Shoulders or arms (eg, shoulder press or bicep curl)	2 sets of 6-15 reps; 10-15 minutes
Balance	—	3-7× per week (3 supervised and 0-4 unsupervised)	4-7/10 RPE	Examples include single leg balance and tandem stance	2 × 30 seconds; 5 minutes
Flexibility	—	3-7× per week (3 supervised and 0-4 unsupervised)	4-7/10 RPE	Examples include hip flexor or quad stretch, hamstring stretch, and chest openers	2 × 20 seconds; 5 minutes
Locoregional	—	3-7× per week (3 supervised and 0-4 unsupervised)	4-7/10 RPE	Surgery-specific resistance and flexibility exercises (eg, swallowing exercises for esophageal participants)	2 × 20 seconds; 3-5 minutes
Cooldown	All sessions will conclude with a 5-minute cooldown to gently return heart rate to resting values (RPE 1-3/10).	—	—	—	—
Progression—aerobic	Sessions will begin at the lower limit of the desired range (eg, 3 sessions at 40% HRR^f^) and progress to the upper limit of the desired range (eg, 7 sessions at 70% HRR) as tolerated.	—	—	—	—
Progression—resistance, balance, and locoregional	Sessions will begin at the lower limit of the desired range (eg, 4/10 RPE) and progress to the upper limit of the desired range (eg, 7/10 RPE) by modifying repetitions, sets, or difficulty of exercises as tolerated.	—	—	—	—

^a^All programs will be tailored to each individual based on their functional level and environment.

^b^RPE: rating of perceived exertion.

^c^Not applicable.

^d^MICT: moderate intensity continuous training.

^e^HIIT; high intensity interval training.

^f^HRR: heart rate reserve.

#### Qualified Exercise Professional Training

Multiple YMCA-qualified exercise professionals will be trained in health coaching and MI to complete this study. This training will include (1) Thrive health services exercise oncology training [21], an exercise oncology-specific asynchronistic training module; (2) Health Coaching Certification [21], an evidence-based training that focuses on empowering health behavior change; and (3) completion of a full-day workshop on study protocol and MI techniques, including talks from experts in the field, individuals with lived experience of lung or esophageal cancer, and other health care professionals. Each counseling session will have a checklist and protocol for qualified exercise professionals to use outlining the targets and goals for each session. All qualified exercise professionals will be overseen by the YMCA clinical exercise physiologist who will offer advice and guidance on movement programming and health coaching sessions.

### Outcome Measures

Feasibility (primary outcome) will include (1) recruitment feasibility—recruitment rate (the number of participants referred per month), enrollment rate (the number of enrolled participants divided by the number of referred participants), reasons for declining, and prehabilitation window (time between consent and surgery); and (2) intervention feasibility (adherence to the movement intervention, attrition, safety, study completion rate, and adverse events). The feasibility target for recruitment is a 25% enrollment rate. The feasibility target for adherence is 70% or more, measured by attendance to movement sessions with the qualified exercise professional. The feasibility target for attrition is 20% or less [22]. A timeline of feasibility measures is available in Table 3.

**Table 3 table3:** Timeline of program measures^a^.

		T0 (baseline)	T1 (before operation)	Surgery	T2 (after operation; weeks 4-6)		T3 (long-term follow-up; week 32)	
**Feasibility and acceptability**								
	Referral rate	✓						
	Referring provider enrollment	✓						
	Referred patient	✓						
	Enrollment rate	✓						
	Adherence		✓		✓		✓	
	Prehabilitation window		✓					
	Safety	✓	✓		✓		✓	
	Reasons for decline	✓						
	Attrition	✓	✓		✓		✓	
**Patient characteristics**								
	Demographic information	✓						
	Cancer (type and stage)	✓						
	Treatment Status	✓						
	Surgery type	✓						
**Resting, physical fitness, and patient-reported outcomes**								
	Height	✓	✓		✓			
	Weight	✓	✓		✓			
	Vitals	✓	✓		✓			
	Pulmonary function	✓	✓		✓			
	5TST^b^	✓	✓		✓			
	Stair-climb test	✓	✓		✓			
	Grip strength	✓	✓		✓			
	FACT-L^c^ or FACT-E^d^	✓	✓		✓		✓	
	FACIT-F^e^	✓	✓		✓		✓	
**Clinical outcomes**								
	Clavien-Dindo Surgical Complication (grade)			✓	✓			
	Postoperative hospital LOS^f^			✓	✓			
	Readmission and ED^g^ visits			✓	✓			
	Mortality			✓	✓			

^a^Pulmonary function test consists of tidal volume, forced vital capacity, vital capacity, and functional residual capacity. Vitals consist of blood pressure and pulse rate.

^b^5TSTS: 5 times sit to stand.

^c^FACT-L: Functional Assessment of Cancer Therapy—Lung.

^d^FACT-E: Functional Assessment of Cancer Therapy—Esophageal.

^e^FACIT-F: Functional Assessment of Chronic Illness Therapy—Fatigue.

^f^LOS: length of stay.

^g^ER: emergency department.

Participant outcome measures will include demographic information (age, sex, gender, socioeconomic status, race, marital status, educational level, and health knowledge), anthropometric measurements (height, weight, and BMI), medical information (surgery type, diagnosis, date of diagnosis, treatment status, and other chronic conditions), and patient-reported outcomes (PROs) that include quality of life (Functional Assessment of Cancer Therapy–Lung or Functional Assessment of Cancer Therapy–Esophageal) [23,24] and fatigue (Functional Assessment of Chronic Illness Therapy–Fatigue) [25]. Both the Functional Assessment of Cancer Therapy–Lung or Functional Assessment of Cancer Therapy–Esophageal and Functional Assessment of Chronic Illness Therapy–Fatigue have been extensively validated and are reliable and widely used tools in the oncology setting [23]. Participants will have the option of completing surveys using the web-based (REDCap [Research Electronic Data Capture]; Vanderbilt University) database or using a pen and paper–based survey. A comprehensive assessment of functionality will be conducted in person in the clinic by the surgeon. Functional assessments are based on the Canadian Society of Exercise Physiology’s Physical Activity Training for Health Protocol and include height, weight, resting heart rate and blood pressure, 5× chair sit-stand, stair climbing test, and grip strength. As part of standard of care, participants will undergo pulmonary function tests; these measures include tidal volume, forced vital capacity, vital capacity, and functional residual capacity.

The participants will be interviewed prior to the commencement of the program to better understand their perception of prehabilitation health coaching and to better understand their history with movement and healthy lifestyle behaviors. This will include questions that are based on past behaviors and future goals. This interview will be audio recorded and transcribed verbatim. A content analysis will be done using the Behavior Change Wheel and Theoretical Domains Frameworks [26,27]. This will aid in better understanding the behavior and barriers or facilitators to engage in the behavior. For sustained behavior change, participants need to have the Capability, Opportunity, and Motivation to perform the behavior [27]. Participants will also be interviewed at the end of the program to better understand their satisfaction with the program. This will also aid in understanding participants’ perceptions of where they are regarding long-term behavior change. Postprogram interviews will be conducted to better understand their perspective on the program and how or if they found the program beneficial; these interviews will probe the understanding of sustained health behavior change and program satisfaction.

Postoperative outcomes include length of hospital stay and postoperative complications. The severity of complications will be graded according to the Clavien-Dindo classification [28,29]. Return to the emergency department within 90 days after the operation and 90-day mortality will also be assessed.

### Statistical Analyses

The statistical analysis for this trial will be conducted with R (R Foundation for Statistical Computing). Participant characteristics will be summarized using descriptive statistics (mean, SD, frequency, and percentage). We will report on reasons for exclusion, attrition, and adverse events with frequency and percentages for each group. Safety will be determined by examining the total number of adverse events that occur over the duration of the program. Adherence to movement sessions will be summarized as a percentage (the number of movement sessions attended divided by the number of available movement sessions).

Baseline demographic and disease-related variables will be compared between prehabilitation and data-only participants using 1-way ANOVA for continuous variables and a chi-square test for categorical variables. The effectiveness analysis will include a linear mixed model to assess the difference in physical fitness and PROs from baseline (T0) to the preoperative (T1), postoperative (T2), 4-6 weeks postoperative (T3), and 32-week long-term follow-up (PROs only) time points, where the time point is the fixed effect and the individual participant is the random effect. A sensitivity analysis will be performed adjusting for sex, surgical type, and age. Linear mixed effect models will also be used to determine between-group differences. An α of .05 will be considered statistically significant. Point estimates and 95% CIs will be calculated for changes in the physical function and PROs at each timepoint and will also be used to provide important information for future sample size calculations. A Poisson regression will be used to estimate differences between groups for postoperative outcomes (ie, length of hospital stays, postoperative complications, return to emergency department, and mortality). Missing outcome data will be imputed using multiple imputation effects. Conclusions will be drawn using comparisons of each time point relative to the baseline.

Qualitative description is used to describe rather than interpret phenomena. Content analysis, the process of making sense of the meaning in the data will also be used during our thematic analysis. The research assistant will work with an experienced qualitative researcher to conduct multiple reviews of the transcripts and tapes (step 1) to familiarize themselves with the data. The analysis will be initiated as soon as the first interview is completed and continued concurrently with data collection. The analysis will examine what individual, structural, cultural, and institutional contexts are hypothesized to affect success. Additional codes will emerge to develop a thematic framework (step 2) that reflects the language and experiences of participants. An audit trial will be used to document the decision-making process. Sections of the transcripts will be charted into themes (step 3). Codes will be combined into themes during a series of research team meetings in which the relationships between behavior and the patient’s capability, opportunity, and motivation to do said behavior will be explored and summarized. Analysts will review the codes and associate themes multiple times to check for potential biases, to ensure they reflect participants’ words, and to improve and validate the interpretation (step 4) of the interviews. Additional interviews may be added when new themes emerge. Initial findings will be shared with a group of participants to help with interpretation and generate meaning from the data.

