#### Enrollment and Assessment

Each potential participant will go through an assessment with the surgeon, including height, weight, blood pressure, heart rate, pulmonary function tests, grip strength, and a stair climb test as part of their clinical assessment. The thoracic surgeon will then raise the subject of prehabilitation with patients. At this point, patients will have the choice to participate in the prehabilitation program or not. If the participants do not agree to the study, they will continue with a standard of care. If a participant agrees to participate and provides written informed consent in accordance with the Nova Scotia Health Research Ethics Board, they will be referred to the research team and YMCA for immediate start of a prehabilitation program. Those who do not participate in prehabilitation will be used as a comparison group, through a waiver of consent; only those as part of the circle of care will pull these deidentified data for the research team.

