#### Intervention

Participants will first have an appointment with a community-based, qualified exercise professional to discuss a tailored prehabilitation program. This will be dependent on a current functional fitness assessment (completed by the surgeon), goals of care, and surgery date. Participants will receive a handbook that will guide them through this process. The handbook will include a calendar of events, a guide to prehabilitation modalities (eg, movement, nutrition, sleep hygiene, stress management, and smoking cessation), publicly available resources (eg, Canada’s Food Guide, CSEP 24-Hour Movement Guidelines, and Smoking Cessation guidelines), and helpful worksheets and other resources (Tobacco Free Nova Scotia Quit Line and mindfulness webinars). Participants will have the choice of delivery modality: either at home, virtual via Zoom (Zoom Video Communications), or at the nearest community-based YMCA. Both in-person and virtual programs will run in the same fashion. All participants will be given 2 resistance bands to assist with their at-home exercises. The intervention will last a total of approximately 8 weeks (Figure 2), depending on the time of surgery and postoperative follow-up. The intervention follows a tailored design, whereby the first 2-3 weeks provide more support, followed by weekly support and then biweekly support. This approach will help contribute to the autonomy of each patient. Following each counseling session, participants will engage in tailored movement sessions.

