#### Health Coaching

Participants will work with a qualified exercise professional who is trained in motivational interviewing (MI) to promote positive lifestyle habits. Participants will meet virtually or in person for counseling and movement sessions. Participants will receive 6 health coaching sessions prior to surgery (approximately 3×/week), with 5 additional wellness sessions after surgery (1×/weekly in the first month), and a follow-up (approximately 4-6 weeks after surgery). Health coaching will last 10-15 minutes, and the aim of these MI-informed behavioral counseling sessions is to develop personalized goals. Through MI techniques, qualified exercise professionals will use a shared decision-making approach with participants to promote evidence-based lifestyle modification, while using publicly available, evidence-informed resources to educate the participant on healthy and positive lifestyle behaviors. Following health coaching, the coach will lead the participant through a 15-45-minute movement routine. The booster sessions will provide health coaching over the phone or via Zoom only (Table 1).

**Table 1 table1:** Overview of health coaching sessions.

Session		Week		Topic		Goal of session

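### Programme safety is determined from an undifferentiated adverse event total over a period that includes surgery, and the per-group adverse event figures are not like for like

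*Protocol article*

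**What the plan says.** Outcome Measures places safety in the primary outcome. Intervention feasibility is listed as "adherence to the movement intervention, attrition, safety, study completion rate, and adverse events". Numerical targets are set for enrollment (25%), adherence (70% or more) and attrition (20% or less), but none for safety.

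Statistical Analyses gives the safety criterion: "Safety will be determined by examining the total number of adverse events that occur over the duration of the program". It also promises a report by group: "We will report on reasons for exclusion, attrition, and adverse events with frequency and percentages for each group".

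On the period, the Intervention section says: "The intervention will last a total of approximately 8 weeks (Figure 2), depending on the time of surgery and postoperative follow-up". The Health Coaching section says: "Participants will receive 6 health coaching sessions prior to surgery (approximately 3×/week), with 5 additional wellness sessions after surgery". Table 1 puts sessions 1-6 in weeks 1-2, opens the surgery block at week 3, and puts sessions 7-11 in weeks 3-8. Boosters follow at weeks 16, 24 and 32.

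Table 3 marks safety at T0, T1, T2 and T3 under the feasibility heading. Under a separate clinical heading it lists Clavien-Dindo grade, length of stay, readmission and emergency visits, and mortality.

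On the comparison group, Enrollment and Assessment says: "Those who do not participate in prehabilitation will be used as a comparison group, through a waiver of consent", and "only those as part of the circle of care will pull these deidentified data for the research team".

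**The concern.** The question for a feasibility study of prehabilitation is whether the movement programme itself causes harm. A single total cannot be read that way when the counting period contains a major operation. A high total may mean only that patients had lung or esophageal surgery. A small excess of exercise-related events can sit within the chance variation of the surgical count. The Introduction itself calls postoperative complications a significant risk in these patients.

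The per-group report has a separate weakness. A coach who meets a participant about 11 times will hear of events that never reach a chart. Decliners have no such contact. They also have no programme, so the counting period in the safety criterion has no start or end for them. A reader who sees the two percentages side by side will compare them, whether or not a test is attached.

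**Working it through.** **1. Denominator.** Participants section: 10 surgical patients a month, 16 months, 25% enrollment, 20% attrition. 10 × 16 × 0.25 = 40 enrolled; 40 × (1 − 0.20) = 32. The stated 32 in the programme is reproduced.

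**2. Does the period contain surgery?** Yes. On Table 1, weeks 1-2 are preoperative and the block from week 3 to week 8 is perioperative or postoperative.

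**3. What the article gives on surgical risk.** It gives no complication rate. The Introduction gives 30-day mortality as high as 10% (lung) and 2.8% (esophageal). With surgery at about week 3, those 30 days fall inside the 8 weeks. As ceilings, 32 × 0.10 = 3.2 deaths and 32 × 0.028 = 0.9 deaths.

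**4. Share of the total due to exercise (assumed rates).** Take the expected number of participants with an event as 32 × rate.

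| Surgical rate | Exercise rate | Surgical | Exercise | Exercise share |
|---|---|---|---|---|
| 50% | 1% | 16.0 | 0.32 | 0.32/16.32 = 2% |
| 20% | 1% | 6.4 | 0.32 | 0.32/6.72 = 5% |
| 50% | 5% | 16.0 | 1.6 | 1.6/17.6 = 9% |
| 20% | 5% | 6.4 | 1.6 | 1.6/8.0 = 20% |
| 10% | 10% | 3.2 | 3.2 | 3.2/6.4 = 50% |

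The last row is an extreme case, included to show that dominance by surgery is not guaranteed. For surgical rates of 20-50%, the binomial SD of the surgical count is √(32 × 0.2 × 0.8) = 2.3 to √(32 × 0.5 × 0.5) = 2.8. The expected 0.3-1.6 exercise-related participants are fewer than that chance variation.

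**5. What a split would show.** If exercise-related events are identified as such, the chance of seeing at least one in 32 at a true rate of 5% is 1 − 0.95³² = 81%. If none is seen, the exact two-sided 95% upper bound is 1 − 0.025^(1/32) = 10.9% per participant.

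**6. Unequal ascertainment (assumed capture).** If true rates are equal and records capture 50-90% of what a coach would hear, the programme group shows an apparent excess of 1/0.9 = 1.1-fold to 1/0.5 = 2.0-fold. The missing programme period for decliners needs no assumption; it follows from the design.

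**The case against.** The strongest reply is that the article never says Clavien-Dindo complications enter the adverse event total. It lists safety and clinical outcomes under different headings in Table 3, and postoperative outcomes have their own Poisson analysis. Adverse event definitions and causality grading commonly sit in a full protocol, which is not shown. This stands as far as it goes: a reader might infer that surgical complications will certainly swamp any exercise harm, and the documents do not support that. They give no rates and do not state the overlap. But the criterion is printed, not omitted. It is a total, and nothing shown keeps surgical events out of it.

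Second, Table 3 marks safety at T0, T1, T2 and T3, so preoperative events can probably be separated. That also stands. It would be wrong to say that a preoperative excess must stay hidden. The data are scheduled in a form that permits the split; the stated criterion does not use it.

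Third, no between-group test of adverse events is planned, only frequencies and percentages. A reader might infer an invalid hypothesis test; there is none. The weakness is in the descriptive comparison.

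Fourth, no safety target is set, so no stated go or no-go decision turns on the total. This limits the consequence but does not make the total informative.

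Finally, an all-cause total avoids unblinded judgement about cause. That is a good reason to keep it alongside the split.

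**Conclusion.** The point holds in limited form. A component of the primary outcome is determined from one undifferentiated count over a period that includes surgery. Followed as written, that count is likely to be mostly surgical and would say little about the safety of the movement programme. The exercise share is about 2-20% if 20-50% have a surgical complication and 1-5% an exercise-related event. These rates are assumptions, and at 10% and 10% the share reaches 50%. The conclusion also depends on surgical complications being counted as adverse events, which the article neither states nor excludes.

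The per-group adverse event figures are not like for like. This follows from the design. Its size (1.1- to 2.0-fold at 50-90% capture) is assumed. The change is worth making in a pilot whose purpose is feasibility, but the documents do not support calling the safety assessment worthless.

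**What to change.** - Keep the all-cause total of adverse events as a descriptive figure.
- Determine programme safety from the number and percentage of programme participants with an adverse event, shown separately before and after surgery and by relation to movement, whether supervised or unsupervised (Table 2 allows both), with exact 95% CIs per participant. A per-session rate is less suitable as the main figure, because sessions cluster within participants and attendance will be incomplete.
- State how Clavien-Dindo complications relate to the adverse event total, so that they can be identified and are not counted twice without notice. Postoperative events judged related to movement should stay visible in the safety table, since sessions resume after surgery.
- Present adverse events for the programme group only. Limit between-group contrasts to outcomes taken from the same chart source over the same window in both groups. The postoperative outcomes already planned (complications, length of stay, emergency return, mortality) can serve if extracted that way.

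The cost is a change of wording and two fields on the adverse event form (phase, and relation to movement). The downsides are some subjectivity in unblinded attribution and the loss of an overall between-group adverse event table. The article reports only 2 participants enrolled in the programme, so on that count little would need to be recoded.

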### Participants

Based on a monthly surgical volume of 10 patients per month to the referring surgeon, assuming an enrollment rate of 25% while accounting for 20% attrition within a 16-month recruitment window, we will seek to recruit 64 participants (aged 18 years and older) diagnosed with lung or esophageal cancer (32 in the program and 32 who decline). This is based on the number of surgical candidates that the current surgeon sees in a 2-year period. Participants will be identified based on the following inclusion criteria: (1) confirmed diagnosis of lung or esophageal cancer; (2) treatment plan includes surgery (at least 2 weeks from the time of consent) [20]; (3) fluent in English; and (4) surgical oncologist approval. Exclusion criteria include (1) unstable or symptomatic cardiac disease, musculoskeletal injury, or comorbid disease that precludes the ability to safely engage in physical activity or (2) significant cognitive limitations.

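### The comparisons with patients who declined are stated without confounder adjustment, and the one adjusted analysis follows a time-only model whose contrasts it can barely move

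*Protocol article*

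**What the plan says.** Group membership is the patient's decision. After the surgeon's assessment, "At this point, patients will have the choice to participate in the prehabilitation program or not". The Enrollment and Assessment section continues: "Those who do not participate in prehabilitation will be used as a comparison group, through a waiver of consent". The Participants section plans "32 in the program and 32 who decline".

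The Statistical Analyses section then proceeds in this order:

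1. "Baseline demographic and disease-related variables will be compared between prehabilitation and data-only participants using 1-way ANOVA", with chi-square tests for categorical variables. No later step uses the result.
2. A linear mixed model for fitness and patient-reported outcomes, with time point as the fixed effect and participant as the random effect. There is no group term.
3. "A sensitivity analysis will be performed adjusting for sex, surgical type, and age".
4. A statement that mixed models will also serve for between-group differences. No covariate is named.
5. Poisson regression for group differences in stay, complications, emergency department return and death. No covariate is named.
6. Multiple imputation of missing outcomes, with conclusions drawn from each time point against baseline.

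The Discussion lists the comparator among the strengths because it allows preliminary effect estimates. It also concedes that lack of randomization may lower internal validity.

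**The concern.** When patients select their own group, case mix can differ between groups for reasons unrelated to the program: cancer site, age, fitness and motivation. A crude group difference then mixes any program effect with the difference in case mix. The plan has one adjusted analysis. By its position, it is attached to the within-person time model, which does not compare the groups at all.

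Two things are at stake. First, the between-group estimates meant to inform later work would be crude ones. Second, the sensitivity analysis would return essentially the main result whether or not confounding is present, and agreement between the two could be reported as robustness.

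**Working it through.** **Sample size, from the Participants section.** Inputs: 10 patients per month, 16 months, 25% enrollment, 20% attrition. 10 × 16 × 0.25 = 40 enrolled; 40 × (1 − 0.20) = 32. The plan's figure reproduces. It is a feasibility number, and with 32 decliners it gives 64 patients to support any adjustment.

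**Why the stated adjustment is inert.** Write the model as y(i,t) = μ + τ(t) + β·x(i) + b(i) + e(i,t), where x(i) holds age, sex and surgical type. If every participant contributes every visit, the estimate of τ(t) − τ(0) is the mean over participants of y(i,t) − y(i,0). Both β·x(i) and b(i) cancel in that difference. Imputing missing outcomes makes each analysed data set complete, so the result then applies.

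In a group-by-time model the contrast is the mean change in the program minus the mean change in decliners, and x(i) cancels again.

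**Numerical check.** Simulated data, 32 per group, 4 visits, residual SD 5, random-intercept model fitted by REML:

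| Quantity | Without covariates | With age, sex, surgery |
|---|---|---|
| Time 1 vs baseline (program arm) | 2.772294 | 2.772294 |
| Time 2 vs baseline | −6.288520 | −6.288520 |
| Time 3 vs baseline | −0.208668 | −0.208668 |
| SE of each | 1.2436 | 1.2436 |
| Group-by-time contrasts | 0.388, 0.545, 1.527 | 0.388, 0.545, 1.527 |
| Group main effect (difference at T0) | −3.24 | −6.26 |

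With 20% of follow-up visits missing at random and not imputed, the time contrasts moved by 0.02 to 0.12 in one data set. Over 60 runs with age-dependent dropout, the largest shift per run averaged 0.13 and reached at most 0.31. These are small against a residual SD of 5, but not zero.

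**Exposure of the Poisson outcomes.** These have no pre-operative value to subtract, so a case-mix difference passes straight into the group ratio. The documents give neither stays nor case mix, so the following are assumptions: mean stay 5 days (lung) and 10 days (esophageal), 10% esophageal in the program, and no program effect.

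- Program mean: 0.1 × 10 + 0.9 × 5 = 5.5 days.
- Decliners 20% esophageal: 0.2 × 10 + 0.8 × 5 = 6.0 days; ratio 5.5 / 6.0 = 0.92.
- Decliners 30% esophageal: 0.3 × 10 + 0.7 × 5 = 6.5 days; ratio 5.5 / 6.5 = 0.85.

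A second illustration uses an assumed frailty factor that multiplies the outcome rate by R. The crude ratio is [1 + p(program)(R − 1)] / [1 + p(decliners)(R − 1)].

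- With 30% vs 50% frail and R = 1.5: 1.15 / 1.25 = 0.92.
- With 30% vs 50% frail and R = 3: 1.6 / 2.0 = 0.80.
- With 20% to 40% frail in the program, 50% among decliners and R from 1.5 to 3: 0.96 to 0.70.

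For 30% vs 50% frail, R of 1.5 to 2 and 32 per group, the simulated type I error of the unadjusted Poisson comparison was 0.16 to 0.38 when non-frail patients had a mean count of 5. It was 0.06 to 0.08 at a mean of 0.5. With the factor in the model it was 0.04 to 0.05.

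**The case against.** **Silence is not a decision.** The article does not say that the between-group models are unadjusted; it lists no covariates, and an analysis plan that is not shown could name them. This is fair, and a reader should not infer that the investigators decided against adjustment. What remains is what the article does fix: it names an adjustment set and places it on the time-only model, ahead of both between-group statements.

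**The sensitivity sentence names no model.** It might be meant to cover the between-group analyses. Its position favors the narrower reading but does not settle the matter. On the wider reading, adjustment would alter the Poisson ratios and the group main effect of a mixed model, so it is too strong to say that the check can never reveal anything. It would still leave contrasts relative to baseline unchanged, and the article draws its conclusions from those.

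**Baseline and site are not ignored.** A reader might infer that the T0 value and cancer site go unused. The documents do not support that. T0 is a response level in the mixed model, and comparing changes from T0 removes stable differences between groups. Surgical type largely stands in for site. In non-randomized groups, neither conditioning on T0 nor comparing changes is generally less biased.

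**Consequences are limited.** Feasibility is primary, the numerical targets concern enrollment, adherence and attrition, and the lack of randomization is acknowledged. This stands and limits the severity. It does not make the stated adjustment informative.

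**Conclusion.** The point holds in this form. The comparator is self-selected, the between-group mixed and Poisson models are stated without confounders, and the only adjusted analysis is placed where it says little about confounding. Invariance is exact for time-constant main effects in a random-intercept model with complete or imputed data, and approximate with unimputed missing visits. Covariate-by-time terms would break it, but none are stated.

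Size and direction of the bias are unknown. The stay ratios of 0.92 to 0.85 and the frailty figures rest entirely on assumed inputs. A reader might infer that the between-group estimates will mainly reflect who accepts, in the program's favor. No passage says which patients decline, so that does not follow.

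This is worth correcting before analysis. It concerns secondary, preliminary estimates and leaves the feasibility conclusions untouched.

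**What to change.** Move the adjustment to the between-group analyses. Report the adjusted result as the main between-group estimate and the unadjusted one second.

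- **Length of stay:** group, cancer site or surgical type, age, and one T0 fitness measure such as the stair climb.
- **Complications and emergency department return:** the same set only as far as the event count allows; otherwise site or surgical type alone, or a single propensity score.
- **Mortality:** report descriptively.
- **Fitness outcomes:** a group-by-time model in which confounders can act on the contrasts. Either keep T0 as a response and add covariate-by-time terms, or condition follow-up values on T0. Name one as main and show the other as sensitivity.
- **Time-only adjusted analysis:** drop it, or reassign it to the models above.
- **Interpretation:** state that unmeasured confounding, motivation included, remains and that the comparisons are preliminary.

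The cost is revised analysis wording, a few degrees of freedom and slightly wider intervals. No new data are needed: Table 3 lists cancer type and surgery type at T0, age is among the demographic items, and the surgeon measures pulmonary function, grip strength and stair climb in every potential participant before the choice is made. With 64 patients and possibly few events, the covariate set must stay short.
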